### Moderation analyses

Sub-aims of this study include examination of mediating pathways to change, and effect modification, i.e., sub-populations for whom the app may be more efficacious. Main effects analyses stratified by intervention group will explore effects underpinning the interaction term. Further stratified analyses will examine key moderators including demographic/background characteristics, violence severity, resilience, and violence-related help-seeking. Effect sizes will be compared between the groups, as the stratified analyses will not be fully powered.

### Statistical power

As decisional conflict estimates were unavailable for target population, the study powers on IPV; 2014 Kenya national data estimate 39% lifetime IPV prevalence for women [12]. Setting alpha = 0.05 and power to .80, a study with 175 intervention participants and 175 controls will find a significant difference between the groups if 25% of women experience violence in the intervention group compared to 39% in the control group [57]. If attrition rate is 15%, we will be able to detect significant difference if 24% of the intervention group experiences IPV.

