### IPV survivor participants in focus group discussions

After informed consent, the majority of the survivors participated in one of six semi-structured FGDs, with an average of eight per group. One survivor opted for an individual interview for privacy. FGD participants had a mean age of 32.3 (SD = 12.6). Approximately 30% identified as Kikuyu and Luhya, with fewer identifying as Luo (14.3%), Kamba (14.3%), Borana (4.1%), and Meru (4.1%). Nearly 80% of women were in a current relationship and had on average two children (SD = 1.6). Almost half (49.0%) of survivors reported past month physical violence and 36.7% reported past month sexual violence.

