### Recruitment of participants

Eligible women were ages 18–35 years-old, had experienced physical or sexual IPV, or reported being afraid of their partner in the last three months, resided in Korogocho/Kariobangi, Dandora, or Huruma/Mathare with no plans to move in the next six months, and spoke English or Swahili language. Community-based recruitment occurred through flyers, community presentations, and word-of-mouth. This passive recruitment method is a sensitive way to recruit IPV survivors, allowing them the opportunity to decide on study participation without feeling pressured.

Local CHVs aided in raising awareness about the study and referring potential participants. Recruitment events held specifically with CHVs informed them of the study objectives and sought feedback on recruiting eligible women. CHVs then worked in tandem with the recruitment team to refer potential participants. Study participants were also offered recruitment flyers to notify others about the study. Recruitment continued until adequate sample size achieved in each of the three sites with an enrollment goal of 350 women. The study process is outlined in Fig. 1.

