Longer-term outcomes focused on IPV experiences. Physical and sexual IPV were assessed through the short forms of the Revised Conflicts and Tactics Scale (CTS-2) [46]. For each of ten violent behaviors, women were asked frequency of occurrence in the past 3 months: Never (0), 1–2 times (1), 3+ times (2), and scores summed across behaviors (Range: 0–20); IPV will be examined as both continuous and binary for physical IPV only, sexual IPV only, and combined physical and sexual IPV. The Women’s Experiences of Abuse (WEB) Scale [47] captured the lived experience of abuse (Responses: 1-Agree Strongly to 6-Disagree Strongly; Range: 10–60). Reproductive coercion was assessed via existing 9-item measure [48, 49] deemed appropriate based on formative research and summarized into a binary measure indicative of experience/no experience. All IPV assessments used behavioral definitions in accordance with best practices [43].

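### The power statement uses a national lifetime IPV prevalence of 39% as the control-group rate for a past-3-month outcome in women enrolled for recent IPV or partner fear

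*Protocol article*

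**What the plan says.** Under Statistical power, the protocol article states "the study powers on IPV; 2014 Kenya national data estimate 39% lifetime IPV prevalence for women". It continues: "Setting alpha = 0.05 and power to .80", "a study with 175 intervention participants and 175 controls" will find a significant difference "if 25% of women experience violence in the intervention group compared to 39% in the control group". For losses to follow-up it adds: "If attrition rate is 15%, we will be able to detect significant difference if 24% of the intervention group experiences IPV".

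The Background section defines the 39%: ever-married women aged 15–49, nationally, who have ever experienced physical or sexual violence from a spouse. The same paragraph says that prevalence is higher still in Nairobi's informal settlements.

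The trial's own population and outcome are defined elsewhere:

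- **Population** (Recruitment of participants): women aged 18–35 in three informal settlements who "had experienced physical or sexual IPV, or reported being afraid of their partner in the last three months".
- **Outcome** (Primary outcomes): for each violent behaviour, "women were asked frequency of occurrence in the past 3 months".
- **Formative data** (IPV survivor participants in focus group discussions): "Almost half (49.0%) of survivors reported past month physical violence", and 36.7% reported past-month sexual violence.

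**The concern.** A control-group rate in a power calculation should be the expected outcome rate in that trial's control arm, over that trial's outcome window. The 39% differs on both counts. It is a lifetime measure, whereas the outcome covers three months. It also describes a general population of ever-married women, whereas this sample was selected for recent violence or fear. The article gives no reason for carrying the figure across.

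IPV is one of the primary endpoints and the only one on which the study is powered. If the IPV result is null, readers will judge it against a detectable effect of 39% versus 25%, or 24%. That effect was calculated for a different population and window.

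**Working it through.** **Inputs from the Statistical power section.** Alpha 0.05 (taken as two-sided, which reproduces the stated figures), power 0.80, 175 per arm, 39% versus 25%. With 15% attrition, 175 × 0.85 = 148.75, or about 149 per arm, and 39% versus 24%.

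**Formula.** Two proportions, pooled variance under the null, no continuity correction, with Δ = p1 − p2 and p̄ = (p1 + p2)/2:

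power = Φ{ [Δ√n − 1.96√(2p̄(1 − p̄))] / √(p1(1 − p1) + p2(1 − p2)) }

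**Reproducing the stated figures.**

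- 39% versus 25%, n = 175: Δ√n = 0.14 × 13.23 = 1.852; null term 1.96 × √(2 × 0.32 × 0.68) = 1.293; denominator 0.652. Φ(0.857) = 80.4%. The required n is 174 per arm.
- 39% versus 24%, n = 149: (1.831 − 1.288)/0.648 = 0.838. Φ(0.838) = 79.9%.

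Both statements are correct for their inputs, so the fault lies only in the 39%.

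**Effect of changing the control rate.** The document gives no three-month follow-up rate for enrolled women, so the rates in the first column are assumptions. The planned effect is expressed on three scales:

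- absolute difference: 39 − 25 = 14 points
- odds ratio: (0.25/0.75)/(0.39/0.61) = 0.52
- risk ratio: 25/39 = 0.64

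| Control rate | Detectable rate (gap), 175/arm | Detectable rate (gap), 149/arm | Power, OR 0.52, 175/arm | Power, RR 0.64, 175/arm | Power, 14 points, 175/arm |
|---|---|---|---|---|---|
| 20% | 9.4% (10.6) | 8.7% (11.3) | 59% | 44% | 98% |
| 30% | 17.3% (12.7) | 16.4% (13.6) | 73% | 65% | 88% |
| 39% (plan) | 25.1% (13.9) | 24.0% (15.0) | 80% | 80% | 80% |
| 50% | 35.2% (14.8) | 34.0% (16.0) | 85% | 93% | 76% |
| 60% | 45.1% (14.9) | 43.8% (16.2) | 86% | 98% | 75% |
| 70% | 55.6% (14.4) | 54.3% (15.7) | 83% | >99% | 78% |
| 80% | 66.8% (13.2) | 65.6% (14.4) | 75% | >99% | 84% |

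Detectable rates are at 80% power; gaps are in percentage points.

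**What the document suggests about the true rate.** In the focus-group sample, 49.0% reported past-month physical violence, so past-3-month physical or sexual IPV in that sample was at least 49.0%. That points above 39%. The sample was small, however (six groups averaging eight women, plus one individual interview). It was recruited on a 12-month criterion that included emotional violence and former partners, had no upper age limit, and was not observed after a control intervention.

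**The case against.** The strongest defence is that little depends on the error. The article openly labels 39% as a lifetime figure. Its arithmetic reproduces. The detectable absolute gap with 149 per arm is 14.4–16.2 points over control rates of 50–80%, against 15.0 as planned. At the planned odds ratio, power is at or above the plan for control rates of 50–70%, and at the planned risk ratio it is higher still. A 14-point effect at a 60% control rate has 68% power with 149 per arm, but the plan's own 39% versus 25% has only 74% at that size, so the control rate accounts for about 6 points of the shortfall. All of this stands. It limits the severity, but it does not supply a basis for the 39%.

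Two stronger readings are tempting, and the document supports neither.

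- A reader might infer that the trial cannot meet a 39% control rate because every participant has recent IPV. In fact feeling unsafe or threatened is enough for entry, and that screening item carries no time window (Informed consent and enrollment). The outcome is measured three months later, after controls have also received safety strategies and referrals. A rate near or below 39% is not excluded.
- A reader might infer that 350 women are too few. Power can rise or fall with the control rate, depending on the scale of the effect, so the table does not show this.

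**Conclusion.** The point holds as a wrong input, not as wrong arithmetic. A national lifetime prevalence stands in for a past-3-month control rate in a selected population, without justification. The stated pairs, 39% versus 25% and 39% versus 24%, therefore do not describe this trial's detectable effect.

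The direction of the error is probable (a true rate above 39%) but not proven. Its size depends on the scale:

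- The detectable absolute gap changes little between control rates of 30% and 80%: about 13–15 points with 175 per arm and 14–16 with 149.
- Power for the odds ratio of 0.52 ranges from 59% to 86% over control rates of 20–80%.
- Power for the risk ratio of 0.64 falls to 44% at a control rate of 20% and is 93% or more from 50% upwards.

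These figures assume a two-sided 5% test comparing two follow-up proportions, as the article's own calculation does. This should be fixed, but it does not call the sample size or the design into question.

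**What to change.** Keep the enrolment goal of 350. Rewrite the Statistical power paragraph as follows:

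- Stop using the 39% lifetime figure as the control rate.
- Say that the past-3-month control rate in eligible women is not known, and give the detectable intervention rate at 80% power over an assumed range on both sides of 39%, for example 20–80%, with and without 15% attrition. The table above supplies the values.
- Say that the detectable absolute gap is fairly stable over 30–80%, while power for a fixed odds ratio or risk ratio is not.
- If a trial-based anchor is wanted, baseline past-3-month IPV prevalence pooled over both arms can inform the range. It should not be presented as the follow-up control rate. The Background section says that the investigative team reviewed IPV prevalence, but not whether the figures were pooled or split by arm, so the source should be stated.

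The cost is one rewritten paragraph and a short table, with no extra participants and no change to outcomes or analysis.

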## Discussion

Our extensive formative phase revealed high feasibility and acceptability of community-partnered technology-based safety planning intervention within Nairobi’s informal settlements, where the high prevalence and health impact of IPV has garnered calls for prevention and response [13]. Moreover it generated necessary refinements to ensure successful implementation that builds on the strengths of this community. Context-specific app refinements included app simplicity, readability and content, particularly layout changes to allow increased visualization of messaging and easier access to safety strategies; these refinements may aid in adaptations to additional settings. The planned RCT has the potential to significantly advance the science of IPV prevention and response in LMIC settings, where the evidence base on mHealth interventions for IPV is in its infancy [58].

In contrast with the higher-income settings in which myPlan was initially developed for confidential, anonymous access, women in our formative phase expressed a preference for facilitated administration of myPlan Kenya. Accordingly, our team trained CHVs to support women in using the app for the first time. An unanticipated but highly relevant outgrowth of the formative phase is that the intervention app is poised to function as an important job aid for CHVs and the other lay professionals that serve as important sources of informal support in global health systems. CHVs’ dual roles as community members and informal leaders [59] render them trusted confidants and sources of information on a range of health topics [59–66]. CHVs and other lay providers are increasingly benefitting from job aids [59], including mobile technology [67] and algorithm-based apps that can enhance decision-making [68]. This app could further be integrated into local professional services, including medical, counseling, and legal, to help disentangle women’s priorities when facing complex decisions.

The impact of the resulting trial, and the scale-up of this approach if found effective, is significant in that mobile connectivity of Kenya is almost at saturation; cell phone access now exceeds 94% in urban areas [12]. This strategy ensures nearly universal access for our target population. Study results will be presented to participating partners, key stakeholders, and the general public health community through dissemination forums, development of lay reports, and peer reviewed publications. The resulting app will be available in both downloadable mobile and web-based versions to maximize options in safe and secure access. To our knowledge myPlan Kenya is the first algorithm-based safety intervention app available in this setting that responds directly to the decisional conflicts faced by women experiencing IPV, and provides tailored safety strategies for responding to partner violence. We believe this will be the first experimental study to evaluate its efficacy in a LMIC, where IPV prevention and response needs are high and available services are often limited.

## Data Availability

The data used during the current study are available from the corresponding author on reasonable request.

## Abbreviations

CESD-R: Center for Epidemiologic Studies Depression Scale
CHV: Community health volunteers
CTS-2: Revised Conflicts and Tactics Scale
DA: Danger Assessment
DCS: Decisional Conflict Scale
FGD: Focus group discussions
IDI: In-depth interview
IPV: Intimate partner violence
IRB: Institutional Review Board
JHU: Johns Hopkins University
KID: Key informant discussions
LMIC: Low and middle-income country
NGO: Non-governmental organization
RCT: Randomized controlled trial
SVAM: Sexual Victimization Attributions Measure
TIC: Trauma-informed care
WEB: Women’s Experiences of Abuse Scale
